### Measurement of plasma lipopolysaccharide

2.14

Plasma LPS levels, used as a marker of intestinal permeability and systemic endotoxin exposure, will be determined using the Pierce™ LAL Chromogenic Endotoxin Quantitation Kit (Thermo Fisher Scientific, Madrid, Spain).

### Short-chain fatty acids

2.15

To determine SCFAs in human feces, we will employ the method described by Wang et al. (42) with some modifications. Fecal samples (200 mg) will be homogenized with 2 mL of 30% aqueous acetonitrile (ACN) and vortexed for 5 min to extract the SCFAs. The suspension will be filtered and centrifuged at 4,000 × g at 4°C for 10 min. Chemical derivatization of SCFAs will be performed by mixing 0.4 mL of the sample supernatant with 0.2 mL of 200 mM 3-nitrophenylhydrazine (NPH) solution and 0.2 mL of a mixture containing 120 mM N-(3-dimethylaminopropyl)-N′-ethylcarbodiimide and 6% pyridine solution, in borosilicate test tubes. The mixture will then be incubated at 40°C for 45 min. An HPLC system (Agilent 1,100) equipped with a quaternary gradient pump, an online degasser, an autosampler, a thermostatically controlled column compartment, and a UV–Vis photodiode array detector will be used. Sample separation will be carried out on an Agilent LiChroCART 150 × 4.6 mm Purospher STAR RP-18e column (5 μm particle size) at a constant flow rate of 0.6 mL/min and a column temperature of 30°C. The mobile phase will consist of water (A) and acetonitrile (B), with gradient elution as follows: 10–40% B from 0 to 15 min, and 40–80% B at 30 min.

### Fecal bile acids

2.16

Bile acids in feces will be analyzed following the method described by Kakiyama et al. (43). Lyophilized stool samples will be suspended in water and heated at 90°C for 10 min. The samples will then undergo ultrasonication, followed by the addition of sodium acetate buffer (100 mM, pH 5.6) containing 15 units of cholylglycine hydrolase and 150 units of sulfatase. This mixture will be incubated at 37°C for 16 h. To terminate the reaction, isopropanol will be added, and the mixture will be reheated at 90°C for 10 min. An internal standard, 50 nmol of nor-deoxycholic acid (norDCA), along with 0.1 N NaOH, will then be added to the mixture. Bile acids will be extracted from the fecal matrix by ultrasonication at room temperature for 1 h. After centrifugation, the supernatant will be transferred to a glass test tube, and the pellet will be washed with 0.1 N NaOH. The combined extract will be applied to a Waters Sep-Pak tC18 cartridge, from which retained bile acids will be eluted with methanol and evaporated to dryness under a nitrogen stream. The extracted unconjugated bile acids will be derivatized to their 24-phenacyl esters by adding 10 mg/mL of triethylamine (TEA) in acetone and 12 mg/mL of phenacyl bromide (2-acetobromophenone) in acetone to the dried extract. This mixture will be heated at 50°C with ultrasonication for 1.5 h. The reaction mixture will be diluted with acetone and applied to a Waters Sep-Pak^®^ silica cartridge. To elute the bile acid 24-phenacyl esters, the column will be washed with acetone, and the collected effluent will be dried under a nitrogen stream. The residue will be resuspended in 82% methanol, filtered through a 0.45 μm filter, and an aliquot will be injected into an HPLC system (Agilent 1,100) equipped with a quaternary gradient pump, an online degasser, an autosampler, a thermostatically controlled column compartment, and a UV–Vis photodiode array detector. A Waters Nova-Pak C18 column (300 × 3.9 mm inner diameter, 4 μm particle size), fitted with a guard column (20 × 3.9 mm inner diameter), will be used for separation and maintained at 32°C. Methanol (82%) will serve as the mobile phase at a constant flow rate of 0.65 mL/min. Individual bile acid 24-phenacyl esters will be detected by monitoring their absorption at 254 nm.

### Plasma metabolome

2.17

Untargeted metabolomics in plasma will be performed using LC-HRMS, applying two complementary chromatographic methods: reversed-phase chromatography (C18 column) for hydrophobic metabolites and hydrophilic interaction chromatography (HILIC) for polar metabolites, following the protocol described by Tabone et al. (44). The LC-HRMS experiments will be conducted on an Ultimate 3,000 chromatographic system (Thermo Fisher Scientific, Courtaboeuf, France) coupled to an Exactive mass spectrometer (Thermo Fisher Scientific). Samples will be mixed with 200 μL of methanol and incubated on ice to precipitate proteins. After centrifugation, the supernatants will be collected and evaporated to dryness under a nitrogen stream using a Turbovap (Caliper Life Science Inc., Roissy, France). The resulting dried extracts will be stored at −80°C until analysis. Dried aliquots will be resuspended in 100 μL of water/acetonitrile (95:5, v/v) with 0.1% formic acid for C18 analysis, or in 100 μL of a mixture of 10 mM ammonium carbonate buffer (pH 10.5) and acetonitrile (40:60, v/v) for ZIC-pHILIC analysis. The tubes will be vortexed, sonicated in an ultrasonic bath for 5 min, and centrifuged again for 10 min. Then, 95 μL of the supernatant will be transferred to 0.2 mL vials and mixed with 5 μL of an internal standard mixture to monitor analytical consistency. Compound separation will be performed using a Hypersil GOLD C18 column (1.9 μm, 2.1 × 150 mm) maintained at 30°C (Thermo Fisher Scientific) or a Sequant ZIC-pHILIC column (5 μm, 2.1 × 150 mm) maintained at 15°C (Merck, Darmstadt, Germany). Metabolomic data processing, metabolite annotation, and pathway analysis will be performed using the Workflow4Metabolomics (W4M) platform. Metabolite annotation will rely on a spectral database based on accurately measured masses and chromatographic retention times and will be confirmed by additional LC–MS/MS experiments. The identified metabolites will be imported into the MetaboAnalyst 4.0 platform for pathway enrichment analysis.

### Machine learning analysis to predict markers of microbiota

2.18

A classification analysis using Random Forest (RF) will be conducted to identify microbiota components associated with AD. For RF classification, we will build 3,000 decision trees. This procedure will be repeated in 30 iterations, using 100 different random seeds. Microbial taxa will be classified based on the mean prediction error across the 30 iterations. Discriminatory variables that are considered important in at least 90% of the 100 seed iterations will be identified (24). Predictor variables will be ranked based on their mean variable importance (e.g., mean decrease in accuracy) across the 30 × 100 random trials. This analysis will allow us to identify and categorize microbiota classifiers for AD in our study population, as previously described in a similarly sized Alzheimer’s patient cohort (24). In parallel, a regression-based gradient boosting model (45) will be developed to predict LPS and butyrate levels, as well as total SCFA content, based on clinical data, diet, physical activity, and microbiota profiles. This model will aggregate 1,000 of decision trees to generate predictions. Trees will be built sequentially, with each tree trained on the residuals from all previous trees, contributing incrementally to the final prediction. Features for each tree will be selected from the full dataset, including variables such as energy intake, macronutrients, micronutrients, and microbiota characteristics.

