**Design:**

This two-phase study will begin with baseline data collection from 60 patients with AD and 60 healthy controls. AI and network-based analyses will identify dietary and microbial variables predictive of disease status. Based on these findings, a personalized supplement will be formulated using dietary components—such as fibers, polyphenols, or fatty acids—targeting microbial taxa and metabolic pathways associated with AD. In the second phase, 60 patients with AD will be randomized (1:1) to receive either the personalized supplement or a standard product for 3 months. Effects on microbial taxa, LPS, short-chain fatty acids (SCFAs), and plasma metabolites will be evaluated before and after the intervention.

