### Network interaction analysis

2.19

To transform data such as microbial taxon abundance, dietary components, physical activity, clinical data, and LPS and butyrate levels, into interactions in a two-dimensional space, recently published and validated artificial intelligence-based methods will be employed (46). Using unsupervised or semi-supervised algorithms, the microbial community structure will be analyzed to identify species that contribute the most informative signals and downweight those containing redundant information, thereby eliminating bias in the resulting network. First, topological measures (e.g., centrality indices) will be incorporated as features in classification and regression problems. This approach will allow the model to be sensitive both to the individual variability of each variable and to its relationships with all others (i.e., other microorganisms). Second, a network will be constructed without assuming linear relationships between microbial taxa or applying standard regularization techniques. Ensemble methods (e.g., Random Forest, XGBoost, or AdaBoost) will be used to infer network connections. These methods enable the prediction of each variable based on all remaining n–1 variables by iteratively looping through them. The result is a matrix quantifying the importance of each variable in predicting all others. Additionally, adjusted R^2^ values will be calculated to estimate how predictable each node (e.g., microbial taxon) is when the values of all its neighboring nodes such as other microbial taxa, dietary variables, exercise, clinical data, LPS, or butyrate are known. This allows us to evaluate the conditional probability of change for each node given the state of its neighbors. The networks will be visualized using the qgraph R package (47) and the Fruchterman–Reingold algorithm (48) which positions nodes with stronger or more numerous connections closer together, while placing those with lower centrality toward the periphery. To assess network stability, we will follow the protocol of Costenbader and Valente (49) Stability indices will be computed for all networks to ensure the robustness of results within the dataset. Cohesion metrics (50) will also be estimated as individual indicators of community complexity, evaluating microbial interconnection. Since high cohesion may indicate that many taxa respond simultaneously to external forces, this metric is a promising candidate for correlating microbial network structure with external parameters.

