
### Supplement design

2.20

Patients will be clustered into distinct groups based on the similarity of their baseline gut microbiota composition, clinical markers, and dietary patterns. Dimensionality reduction techniques, e.g., principal component analysis (PCA) or uniform manifold approximation and projection (UMAP) will be applied to reduce noise and identify key features driving interindividual variability. Subsequently, unsupervised clustering algorithms (e.g., k-means, hierarchical clustering, or model-based clustering) will be employed to classify patients into homogeneous subgroups. These patient clusters will serve as the basis for subsequent supplement design, analyses of intervention response and biomarker discovery. The dietary supplement will be formulated by selecting two or three food groups or food components that meet the highest number of predefined criteria. The selection criteria will be: (1) components positively associated with, or predictive of, a greater number of protective variables or markers of healthier status in Alzheimer’s patients; (2) components negatively associated with, or predictive of, a greater number of disease-related markers.

The rationale for designing a supplement rather than recommending dietary modifications is to minimize disruption of habitual dietary patterns, thereby maximizing adherence to the intervention and reducing caregiver burden. In addition to supplement formulation, dietary recommendations may be provided to reduce or eliminate food components associated with unfavorable biomarkers (e.g., predictors of elevated LPS levels or other parameters of disease progression). If lack of physical activity is identified as a relevant factor, tailored recommendations will also be considered according to the patients’ physical condition.

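### Stability over random seeds does not show that an AD marker would recur in other participants, and adjusted R² is not a valid predictability score for tree ensembles

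*Protocol article*

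**What the plan says.** The Abstract (Design) plans "baseline data collection from 60 patients with AD and 60 healthy controls".

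For the random-forest classification of AD, the section on machine learning analysis says "we will build 3,000 decision trees" and then "This procedure will be repeated in 30 iterations, using 100 different random seeds". Markers are retained by this rule: "Discriminatory variables that are considered important in at least 90% of the 100 seed iterations will be identified". They are ordered as follows: "Predictor variables will be ranked based on their mean variable importance (e.g., mean decrease in accuracy) across the 30 × 100 random trials". No cutoff for *important* is given. Mean prediction error over the 30 iterations is mentioned, but not as a condition for keeping a marker.

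The section on network interaction analysis is a separate step. It infers connections with tree ensembles such as random forest, XGBoost or AdaBoost: "These methods enable the prediction of each variable based on all remaining n–1 variables" (n here is the number of variables). Standard regularization is expressly not applied. Of adjusted R² it says that "values will be calculated to estimate how predictable each node (e.g., microbial taxon) is" once the values of the neighbouring nodes are known. Network stability is checked within the same dataset.

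The section on supplement design selects two or three food groups or components by counting. The first criterion is "components positively associated with, or predictive of, a greater number of protective variables", and the second is the mirror image for disease-related markers.

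**The concern.** A marker list that shapes a product should hold up in people other than those in whom it was found. Changing the seed does not test that. It redraws the bootstrap samples and candidate splits inside the algorithm, while the participants and their labels stay fixed. A taxon that happens to differ between these 60 patients and these 60 controls differs in every run. More trees and more repeats make its importance steadier, so the filter becomes easier for chance features to pass.

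Adjusted R² has a related weakness. Its correction counts fitted coefficients in a linear model. A forest or boosted ensemble has no such count, so the correction does not remove the optimism of the fit.

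At stake is the quality of the marker list and of the predictability scores. Both can feed the ingredient count and hence the composition of the supplement compared in the third stage.

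**Working it through.** **Inputs from the article.** 60 + 60 = 120 participants, 3,000 trees, 100 seeds, retention at 90% of seeds, and mean decrease in accuracy as the example importance measure. The article states no performance or error figure for this selection step, so there is none to reproduce. Its one design calculation, 25 per group, concerns a single pre-chosen genus.

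**Assumed, because not stated.** The number of features (300 in the simulation; several values for adjusted R²) and the meaning of *important* (four readings tried).

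**Step 1: the seed rule on pure noise.** 120 participants (60/60), 300 independent lognormal features unrelated to the label, 3,000 trees, out-of-bag mean decrease in accuracy, and 100 seeds on fixed data. Features passing in at least 90% of seeds, in four simulated datasets:

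| Reading of *important* | Features passing, of 300 |
|---|---|
| importance above 0 | 23, 25, 23, 30 |
| above the absolute value of the most negative importance | 7, 9, 5, 6 |
| among the top 10 | 5, 5, 5, 6 |
| among the top 20 | 7, 13, 11, 8 |

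Out-of-bag error in these datasets was 0.50 to 0.59, no better than chance. Importances from two different seeds still correlated 0.74 to 0.85. The seeds agree with each other although there is nothing to find.

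The simulation used one forest per seed. Averaging 30 forests per seed would make noise features more stable, not less.

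**Step 2: contrast with a null reference.** In the first two datasets, *important* was redefined as exceeding the largest importance among 300 permuted shadow features, reshuffled in each of 25 runs. Then 0 and 1 noise features reached 90%, against 23 and 25 when importance above 0 was enough.

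**Step 3: contrast with resampled participants.** A smaller noise run (200 features, 1,500 trees, 10 seeds, impurity importance, top 20) kept 15 of 20 features across seeds but only 3 to 5 of 20 across 80% subsamples of participants. Neither that measure nor the top-20 cutoff is in the article, so this shows direction only. It also shows that resampling without a null still lets some noise through.

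**Step 4: adjusted R².** The formula is 1 − (1 − R²)(n − 1)/(n − p − 1), with n participants and p predictors.

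- n = 120, p = 200, R² = 0.3: 1 − 0.7 × 119/(−81) = 2.03.
- n = 120, p = 200, R² = 0.9: 1 − 0.1 × 119/(−81) = 1.15. The worse fit gets the higher score.
- n = 120, p = 119: the denominator is 0 and there is no value. With patients only (n = 60) this happens at p = 59.
- n = 120, p = 30, random forest on noise: in-sample R² is 0.86, so 1 − 0.14 × 119/89 = 0.81. Out-of-bag R² on the same data is −0.05.

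Feeding out-of-bag R² into the formula does not rescue it. On noise with n = 120 and p = 300, out-of-bag R² is −0.02 and the adjusted value is 1 + 1.02 × 119/181 = 1.67.

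**The case against.** **The method is taken from a cited study, and details may sit in a fuller document.** What the 30 iterations vary is not stated, and they could include data splitting. An article may also leave permutation nulls and cross-validation to a SAP. This stands as a limit: the conclusion applies to the procedure as written. But the point concerns a rule the article does fix, since the 90% is counted over seeds.

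**The amount of noise that passes depends on an unstated cutoff.** This stands. The range is 5 to 30 of 300 under plain readings and 0 to 1 under a shadow-feature cutoff. No single figure can be claimed.

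**The predictor count is not given, and adjusted R² is tied to neighbouring nodes.** This stands as far as values above 1 are concerned, because with a small neighbour set they would not arise. The degrees-of-freedom problem remains, as the case with 30 predictors shows.

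**Stronger readings a reader might infer, which the article does not support:**
- That the seed-selected taxa are scored by adjusted R². They are ranked by variable importance; adjusted R² belongs to the network nodes.
- That adjusted R² is undefined whenever predictors outnumber participants. It is undefined only at p = n − 1. Beyond that it returns a number above 1 without meaning.
- That the whole third stage rests on these selections. LPS and butyrate are named in advance and modelled by gradient boosting without a seed rule. The ingredient criteria also admit simple associations, and the statistical section applies false-discovery-rate control to the high-dimensional domains.
- That the randomized comparison is biased. A weak marker list may give a poor supplement, but it does not distort the comparison between arms. The authors also call the study exploratory.

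**Conclusion.** The concern holds in a limited form. The 90% rule, as written, measures reproducibility of the algorithm and not of the finding, and nothing in the article stops markers from being kept when prediction error is at chance. The size of the effect rests on an assumed 300 independent features and one forest per seed. The mechanism needs neither assumption.

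Adjusted R² should not be used for tree ensembles on either reading of the predictor set. It is uninterpretable if predictors exceed participants, which is plausible with species-level profiles plus diet and clinical variables but is not stated, and it is badly inflated even with 30 predictors.

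Both outputs are only part of what can enter the ingredient count. The change is worth making before the recipe is fixed; it does not threaten the validity of the randomized comparison.

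**What to change.** 1. Count the 90% over resampled participants instead of seeds, for example 100 stratified subsamples. Keep any patient and caregiver-control pair together.
2. Define *important* as exceeding a null reference, from label permutation or shadow features.
3. Report out-of-bag or cross-validated accuracy against that null next to the marker list. If it is at chance, label the markers as unsupported wherever they enter the ingredient count. Labelling is preferable to a rule that declares no marker, which would leave the third stage without a defined product.
4. Replace adjusted R² by out-of-bag or cross-validated R² in the network analysis, and use the same measure for the gradient-boosting models of LPS, butyrate and total SCFA.

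The cost is more computing time and some rewording, with no new data. The downside is that fewer markers are likely to qualify. The subsample number and the choice of null are matters of judgement and should be fixed before the baseline data are analysed.

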### Network interaction analysis

2.19

To transform data such as microbial taxon abundance, dietary components, physical activity, clinical data, and LPS and butyrate levels, into interactions in a two-dimensional space, recently published and validated artificial intelligence-based methods will be employed (46). Using unsupervised or semi-supervised algorithms, the microbial community structure will be analyzed to identify species that contribute the most informative signals and downweight those containing redundant information, thereby eliminating bias in the resulting network. First, topological measures (e.g., centrality indices) will be incorporated as features in classification and regression problems. This approach will allow the model to be sensitive both to the individual variability of each variable and to its relationships with all others (i.e., other microorganisms). Second, a network will be constructed without assuming linear relationships between microbial taxa or applying standard regularization techniques. Ensemble methods (e.g., Random Forest, XGBoost, or AdaBoost) will be used to infer network connections. These methods enable the prediction of each variable based on all remaining n–1 variables by iteratively looping through them. The result is a matrix quantifying the importance of each variable in predicting all others. Additionally, adjusted R^2^ values will be calculated to estimate how predictable each node (e.g., microbial taxon) is when the values of all its neighboring nodes such as other microbial taxa, dietary variables, exercise, clinical data, LPS, or butyrate are known. This allows us to evaluate the conditional probability of change for each node given the state of its neighbors. The networks will be visualized using the qgraph R package (47) and the Fruchterman–Reingold algorithm (48) which positions nodes with stronger or more numerous connections closer together, while placing those with lower centrality toward the periphery. To assess network stability, we will follow the protocol of Costenbader and Valente (49) Stability indices will be computed for all networks to ensure the robustness of results within the dataset. Cohesion metrics (50) will also be estimated as individual indicators of community complexity, evaluating microbial interconnection. Since high cohesion may indicate that many taxa respond simultaneously to external forces, this metric is a promising candidate for correlating microbial network structure with external parameters.
